### Patients’ experience measures

Patient reported perceptions of safety and overall hospital experience will be calculated using the following validated tools (i) Patient Measure of Safety Questionnaire [61] and (ii) the Friends and Family Test [62].

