### Nurses’ experience measures

Registered and enrolled nurses’ perceptions of safety attitudes, organisational readiness to change, barriers to physical assessment, staff engagement and multidisciplinary collaboration will be quantified using the following validated tools: (i) Safety Attitudes Questionnaire Short Form (Teamwork Climate and Safety Climate subscales) [63], (ii) Organisational Readiness to Change Assessment (Context Assessment subscales) [64], (iii) Barriers to Nurses’ use of Physical Assessment Scale [65], (iv) Utrecht Work Engagement Scale-17 [66], and (v) Interprofessional Collaboration Scale [67].

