### Medical officer’ experience measures

Medical officers’ perceptions of safety attitudes and multidisciplinary collaboration will be measured using the following validated tools (i) Safety Attitudes Questionnaire Short Form [63] and (ii) Interprofessional Collaboration Scale [67].

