Patient, nurse and medical officer experience measures will be reported as means and standard deviations of overall component scores, and changes from pre- to post-intervention will be tested using a GLMM with a Poisson link function adjusting for respondent age, tenure (if appropriate) and correlation within ward. We will conduct secondary analyses: i) to investigate changes in outcomes over time, ii) perform the above with additional fixed effects for patient demographics (age, sex, comorbidity), and iii) model differences in primary outcome components by level of comorbidity. A statistical analysis plan pre-specifying all analyses will be formulated and finalized prior to the study data lock.

All analysis will be conducted in the R language for statistical computing, using the lme4 package for generalised linear mixed models [69].

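### Questionnaire scores are to be tested with a Poisson mixed model, so the p-values of the survey secondary outcomes depend on how each score is scaled

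*Protocol article*

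**What the plan says.** The Data analysis section of the protocol article states that "experience measures will be reported as means and standard deviations of overall component scores". It then names the test: "changes from pre- to post-intervention will be tested using a GLMM with a Poisson link function", with adjustment for respondent age, for tenure where appropriate, and for correlation within ward. It names R and lme4 as the software.

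The outcomes concerned are listed under Outcome measures. There are two patient tools, five nurse tools (among them the "Utrecht Work Engagement Scale-17") and two medical officer tools. All are questionnaires. None is a count of events over an exposure time.

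The same Data analysis section separately assigns Poisson regression, with time on ward as the offset, to the patient event data. For the survey scores it mentions no dispersion parameter, robust variance, observation-level random effect or alternative family.

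**The concern.** A Poisson model has no free residual variance: the variance is the mean. For event counts that is a reasonable starting point. For a questionnaire score, the ratio of variance to mean depends on how the items are combined. If every score is multiplied by c, the log ratio of post to pre is unchanged, but the model's standard error is divided by √c and the z-statistic is multiplied by √c. The same answers from the same respondents can then be significant or not according to whether items are averaged or summed.

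The ward random effect does not repair this, because the misfit lies between respondents within a ward.

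The tests of the patient, nurse and medical officer experience measures are at stake. These are named secondary outcomes, and the article's Conclusion counts better clinician and patient experience among the benefits of an effective intervention. A real change could be missed or a chance change declared, depending on the instrument.

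**Working it through.** The article states no power, mean, SD or scoring rule for any survey score, so there is no figure of its own to reproduce. Every mean and SD below is an assumption.

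**Formulae.** Take n respondents before and n after, common mean m and true SD s.
- Poisson model SE of the log ratio: √(2/(n·m)).
- True SE: (s/m)·√(2/n).
- Ratio of model SE to true SE: R = √m / s.
- Actual two-sided error at nominal 5%: 2·[1 − Φ(1.96·R)].
- Power where a correct test has 80%: Φ(2.80 − 1.96·R).

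**Results.**

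| Assumed scoring | Mean | SD | R | Actual error | Power in place of 80% |
|---|---|---|---|---|---|
| Item average | 4 | 1.0 | 2.00 | 0.009% | 13% |
| Item average | 4 | 0.7 | 2.86 | about 0 | 0.3% |
| Sum of six 1–5 items | 22.8 | 4.2 | 1.14 | 2.6% | 72% |
| 0–100 | 70 | 15 | 0.56 | 27% | error not held |
| 0–100 | 70 | 20 | 0.42 | 41% | error not held |

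Example: √4/1.0 = 2.00, so the error is 2·[1 − Φ(3.92)] = 0.00009 and the power is Φ(2.80 − 3.92) = Φ(−1.12) = 0.13. For 0–100 with SD 20, √70/20 = 0.42 and 2·[1 − Φ(0.82)] = 0.41. Over a wider range of 0–100 scores, the error runs from 10% (mean 70, SD 10) to 54% (mean 60, SD 25).

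**Scaling alone.** Suppose 17 items are scored 0–6. As an average (mean 4.0, SD 1.1), R = √4.0/1.1 = 1.82 and the error is 0.04%. The same answers summed (mean 4.0 × 17 = 68, SD 1.1 × 17 = 18.7) give R = √68/18.7 = 0.44 and an error of 39%.

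**Simulation under no effect.** This was a simple before–after comparison, not the full stepped-wedge schedule. It used 24 wards (the planned number), with 20 respondents per ward before and 20 after, ward ICC 0.05, and scores of mean 3.8 and SD 0.7 held within 1–5.
- Poisson random-intercept model, 1,000 runs: rejection rate 0% on the 1–5 average, 2.5% on the same scores times 6, and 35% after conversion to 0–100.
- Simple Poisson contrast, three sets of 20,000 runs: 0% on 1–5 and 32% on 0–100.
- Gaussian contrast with estimated within-ward variance: 4.9–5.1% in the three large sets. It was 7.0% in the 1,000-run set, which is too small to settle the second figure. This test statistic does not change under linear rescaling.

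**The case against.** The strongest objection is that the wording concerns a link, and a log link with another family would not fix the variance at the mean. That is a possible reading, and the variance argument depends on rejecting it. The Poisson family is still the natural reading, given the Poisson regression specified just before it and the lme4 software. On either reading the sentence needs correcting, because no valid test model is named.

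A reader might infer that every survey standard error is badly wrong, with each outcome either untestable or falsely significant. The article does not support that. It gives no scoring for any instrument, and the six-item sum shows a case where little harm is done.

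A reader might also infer that the scores are item averages and so not integers. The article speaks of "will be reported as means and standard deviations of overall component scores", which describes a summary across respondents and does not say how one respondent's score is formed. Summed item scores would be integers.

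The scope is limited. The primary composite and its components are event counts, and neither the stated power nor the cost–benefit analysis uses the survey scores. The descriptive means and SDs remain valid. The promised statistical analysis plan is not shown and may already name another model. That does not cancel the test that the article itself commits to.

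**Conclusion.** The point holds as a defect in the named model. If the Poisson family is meant and no dispersion is estimated, standard errors and p-values for the survey outcomes depend on scoring. Under the assumed means and SDs, the consequence runs from almost no power (item averages), through mild conservatism (a short sum), to 27–41% false positives (0–100 scores). Which of these applies to which instrument cannot be told from the article. This should be fixed, but it concerns secondary survey outcomes only and does not threaten the primary analysis.

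**What to change.** Replace the phrase about a Poisson link with a model that names its family and link and estimates the residual variance. A suitable choice is a linear mixed model (Gaussian, identity link) with a random effect for ward, keeping the planned adjustment for respondent age and tenure and reporting mean differences with 95% confidence intervals. Use an ordinal model for any single-item rating. Other models that estimate the dispersion, such as a beta-type model for bounded scores, would also remove the problem.

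The cost is one sentence, settled before data lock. No new data are needed, and the linear model is available as lmer in the lme4 package already named.

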### Experience measures surveys (patient, nurse, medical officer)

Prior to each step and at the conclusion of the trial, patient, nurse, and medical officer experience measures will be obtained via paper-based self-administered surveys. Surveys will be distributed to intervention ward participants by site leads or ward-level clinical champions. For patients who have vision or physical impairments, but otherwise are eligible and willing to participate, site leads or caregivers may provide assistance in completing the survey. Return of completed surveys will constitute informed consent. Surveys will also contain some brief demographic questions: patient surveys will ask time on ward, age, sex, previous admission history and the 0–100 overall health visual analogue scale from the EuroQol 5-Dimensions Questionnaire [68]; nurse and medical officer surveys will ask their position title and how long they have worked on the participating ward.

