## Data analysis

We expect to collect data from 48,960 patient episodes of care representing 244,800 bed days. With this sample, and with assumptions based on unpublished data for falls occasioning harm, pressure injuries and rapid response calls (intra-cluster correlation = 0.03–0.08, baseline rate = 2–8 incidents/1000 bed days) we will be powered to detect difference in the rate of incidents of 12–28% from pre- to post-intervention [30].

The data analysis period will extend across 68 weeks, comprising 51-week trial period and an additional 17-week control period prior to the first step (Fig. 2). All patients admitted or transferred to one of the study wards during the trial period will be included in the primary analysis. While outcome data are collected continuously, for analysis, time will be categorised per week. Days in weeks prior to the ward commencing the intervention will be counted as pre-intervention, with the exception of the three weeks immediately prior which will be omitted from the analysis as a period for implementation of the intervention (one week of nurses’ education workshops and two weeks of preparation). The three-year set of pre-trial primary outcome data will be used to investigate seasonal or temporal effects, or unusual variations in routinely collected data. Patient age, sex, comorbidity information and admission/transfer data will be used to adjust for variation in patient demographics between wards.

Patient outcome data will be modelled as counts using Poisson regression with an offset for time on ward. Using a Generalised Linear Mixed Model (GLMM) approach, we will use fixed effects for secular trend, and a random effect for ward. The primary outcome will be a composite measure of: (i) medical emergency team calls (inclusive of both rapid response system and ‘Code Blue’ calls); (ii) unplanned intensive care unit admissions; (iii) in-hospital falls; and (iv) hospital-acquired pressure injuries.

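### The survey outcome models carry no term for survey round, so in this stepped-wedge part of any calendar drift enters the estimated pre-to-post effect on these secondary outcomes

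*Protocol article*

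**What the plan says.** The Data analysis section gives one model for all three respondent groups. Scores are summarised first: "Patient, nurse and medical officer experience measures will be reported as means and standard deviations of overall component scores". The test follows: "changes from pre- to post-intervention will be tested using a GLMM with a Poisson link function". The terms that this model is said to contain are then listed in full: "adjusting for respondent age, tenure (if appropriate) and correlation within ward". No term for time, period or round is named.

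The same section treats the event outcomes differently. There, "Patient outcome data will be modelled as counts using Poisson regression with an offset for time on ward", and for that model "we will use fixed effects for secular trend, and a random effect for ward".

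Time appears once more near the survey model, as an aim of the secondary analyses: "to investigate changes in outcomes over time".

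On timing, the section on experience measures surveys says: "Prior to each step and at the conclusion of the trial, patient, nurse, and medical officer experience measures will be obtained". The Design section has three periods of 17 weeks, 51 weeks in all, with 24 wards. On respondent details, patient surveys ask age among other items, while "nurse and medical officer surveys will ask their position title and how long they have worked on the participating ward".

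**The concern.** In a stepped-wedge each ward moves from control to intervention and stays there, so its post-intervention surveys always come later than its pre-intervention surveys. A model with only a pre/post indicator and a ward effect cannot tell the intervention from anything else that changed over the year. Randomising the step order helps the survey estimate only if the model compares exposed and unexposed wards at the same calendar time, and that needs a round term.

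At stake are all the patient, nurse and medical officer experience measures listed as secondary outcomes. Drift towards better scores could make an inert intervention look helpful, and drift the other way could hide a real benefit.

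A smaller matter sits in the same sentence. It names respondent age for all three groups, but the survey section lists age among the questions for patients only.

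**Working it through.** The article states no sample size, effect size or drift for the surveys, so there is no figure of its own to reproduce. The check asks what the stated model returns when the true effect is zero and scores drift.

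**Inputs from the article.** Three steps 17 weeks apart (Design), with surveys before each step and at the end, so four rounds at about weeks 0, 17, 34 and 51; 24 wards.

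**Assumptions.** Eight wards per sequence (Fig. 2 is not shown). All wards answer all four rounds. Drift is linear, d SD per round. For the false-positive rates, 10 or 20 respondents per ward per round, and an intra-cluster correlation (ICC) of 0.03–0.08, which the article gives for patient events and which is borrowed here. A linear model stands in for the planned mixed model.

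**Exposure pattern (0 = pre, 1 = post).**

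| Sequence | wk 0 | wk 17 | wk 34 | wk 51 |
|---|---|---|---|---|
| 1 | 0 | 1 | 1 | 1 |
| 2 | 0 | 0 | 1 | 1 |
| 3 | 0 | 0 | 0 | 1 |

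**Step 1: crude comparison.**
- Mean pre time = (0 + 0 + 17 + 0 + 17 + 34)/6 = 68/6 = 11.3 weeks.
- Mean post time = (17 + 34 + 51 + 34 + 51 + 51)/6 = 238/6 = 39.7 weeks.
- Gap = 28.3 weeks = 28.3/17 = 1.67 rounds, so the bias is 1.67d.

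**Step 2: within-ward comparison.** The slope of time on the post indicator, with ward effects, is the sum of within-sequence cross-products over the sum of squares. Mean time is 25.5 weeks in every sequence.
- Cross-products: (102 − 3×25.5) + (85 − 2×25.5) + (51 − 1×25.5) = 25.5 + 34 + 25.5 = 85.
- Sums of squares: 0.75 + 1 + 0.75 = 2.5.
- Slope = 85/2.5 = 34 weeks = 2.0 rounds, so the bias is 2.0d.

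A ward random effect lies between these limits: 1.84d to 1.95d over the assumed ICCs and respondent numbers. Total drift over the trial is 3d, so the share entering the estimate is 1.67/3 = 56% to 2.0/3 = 67%.

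**Step 3: size.**

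| Drift d per round (assumed) | False effect, 1.67d to 2.0d | Rejection rate at nominal 5%, no round term |
|---|---|---|
| 0.025 SD | 0.04–0.05 SD | 11–18% |
| 0.05 SD | 0.08–0.10 SD | 28–54% |
| 0.10 SD | 0.17–0.20 SD | 79–98% |

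**Step 4: with a categorical round effect.** The bias is 0 and the rejection rate is 5% throughout. The standard error rises from 0.066–0.067 to 0.107–0.110 SD with 10 respondents, and from 0.047–0.048 to 0.079–0.080 SD with 20. Before rounding, the ratios run from 1.61 to 1.69.

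**Step 5: the other possible schedule.** Suppose each ward is surveyed only before its own step and at trial end. The mean pre-to-post gap is (51 + 34 + 17)/3 = 34 weeks, again 2.0d. All post responses then fall in the last round and no pre responses do, so the treatment indicator equals the last-round indicator. The design matrix with intercept, treatment and three round terms has rank 4 for 5 columns, so categorical round effects cannot be separated from treatment.

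**The case against.** The strongest reply is that the article is condensed and its one-line model descriptions are not exhaustive. The count-model sentence names no intervention effect, yet that model must contain one, so an unnamed term is not thereby excluded. A full analysis plan is promised before data lock, and the secondary analyses include change over time.

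Part of this stands: the promised plan could add the term, and the article does not ignore time altogether. But the survey sentence names its contrast and its adjusters, and the count model beside it names a secular trend. The secular-trend wording belongs to event counts with a time-on-ward offset. A separate look at changes over time does not adjust the pre-to-post test. Followed as written, the survey model is biased whenever scores drift in a sustained direction.

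Three stronger readings are tempting, and the article does not support them.
- A reader might infer that all drift is credited to the intervention. For linear drift it is 56–67% of the total, and non-monotone patterns may partly cancel.
- A reader might infer that the trial's main result is compromised. The primary outcome model includes a secular trend.
- A reader might infer that the age adjustment shows an unworkable staff model. The natural reading is age for patients and tenure for staff, which makes this a wording point.

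It is also fair to say that the article shows no evidence that these scores do drift.

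**Conclusion.** The point holds for the survey outcomes and should be fixed. It concerns secondary outcomes only. As stated, the model lets a linear drift of d per round appear as an effect of about 1.67d to 2.0d if all wards answer all four rounds. The multiplier follows from the schedule alone. The effect sizes in SD units rest on assumed drifts, and the rejection rates rest also on assumed respondent numbers and a borrowed ICC.

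Whether the remedy is purely analytical depends on which wards are surveyed in each round. The visible text does not settle this, and Fig. 2, which may, is not shown.

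**What to change.** - **Model.** Add a fixed effect for survey round (four levels) to every patient, nurse and medical officer survey model, and keep the ward random effect. Ward-by-round random effects are optional.
- **Schedule.** State that all 24 wards are surveyed at all four rounds. At the least, wards in different exposure states must be surveyed in the same round.
- **If that is not the schedule.** Where each ward is surveyed only before its own step and at the end, report the survey changes as uncontrolled before-after comparisons, not as intervention effects.
- **Covariates.** Reconcile the two sections: use age in the patient model, and tenure and position title in the staff models.

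**Cost.** If all wards are already surveyed each round, the change is analysis-plan wording plus a wider interval, with a standard error about 60–69% larger in the illustration. Most of that loss arises because round and exposure are correlated, not from the three extra parameters as such. If they are not, surveying all wards every round means extra fieldwork in three respondent groups.

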### Design

A pragmatic, hybrid type 1, stepped-wedge cluster randomised trial design will be conducted [32] with a cost–benefit analysis and qualitative process evaluation. The hybrid type 1 trial design allows the evaluation of intervention implementation concurrent to the primary clinical efficacy outcomes. Combining these data produces more useful information for decision-makers aiming to promote the more rapid translation of evidence to practice [33]. As our trial involves enhancement of current best practice, a stepped-wedge design is desirable as all participants eventually receive the intervention. The trial intervention, implementation and evaluation are informed by the Medical Research Council Framework for complex interventions [34] and evidence-based implementation strategies [35].

The trial intervention will be sequentially implemented over three periods of 17 weeks, totalling 51 weeks. A total of 24 wards will be enrolled to the trial, with eight sites each contributing three wards (Fig. 2).

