### Randomisation

Wards will be stratified by hospital and randomly allocated to one of the three sequences. Planned stratified allocation is shown in Fig. 2. Randomisation will be computer-generated and performed by a blinded researcher not involved in the trial.

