**Fig. 3 Fig3:**
[figure not shown]
Cascading facilitation flowchart

Each participating hospital will nominate an internal nursing staff member to act as the site lead responsible for implementing the trial at their local site. Site leads will be nurses in an existing higher-grade position or senior clinical nurses who have high influence amongst the nursing discipline, with experience in nurse education and facilitating clinical practice change. Responsibilities will include: (i) engaging with nursing and medical management teams and presenting trial overviews, (ii) delivering nurses’ education workshops and additional top-up training as required, and (iii) supporting nursing unit managers to iteratively co-design their ward action plan with the ward clinicians to implement and embed the intervention.

A one and a half-day in-person train-the-trainer workshop with the site leads will be conducted two months prior to the start of the trial. Site leads will be briefed on the overall trial design, the intervention components, and their role within the trial, in particular, proposed engagement processes and training for delivering the nurses’ education workshops. The research team will remotely provide training, support, and resources for site leads to deliver the intervention and engage with site-specific stakeholders. Resources will include the workshop teaching material (PowerPoint presentation, demonstrative videos, and learning handouts), action plan templates, posters and lanyard cards to use as reminders on the ward, and intervention guides for optional internal audits.

Prior to and during the trial, all site leads will meet fortnightly with the research team via videoconference as a learning collaborative group to share progress, report risks, and discuss strategies for navigating barriers. Determined per site, regular internal meetings will be organised by the site lead to maintain engagement and support nursing unit managers (e.g., weekly to fortnightly action plan meetings with nursing unit managers and monthly progress reports with directors of nursing).

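### Read as a single constant effect, the primary estimate gives the longest exposure a negative weight, so a growing effect is diluted and a fading one overstated; secondary analysis (i) should be defined by time since start

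*Protocol article*

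**What the plan says.** All places are in the protocol article.

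- **Layout (Design, Randomisation, Data analysis).** There are 24 wards, "with eight sites each contributing three wards". "Wards will be stratified by hospital and randomly allocated to one of the three sequences". The intervention "will be sequentially implemented over three periods of 17 weeks, totalling 51 weeks", and the analysis window is 68 weeks, "comprising 51-week trial period and an additional 17-week control period prior to the first step".
- **Exposure coding (Data analysis).** "Days in weeks prior to the ward commencing the intervention will be counted as pre-intervention", except that the three weeks before each ward's start are dropped. No weeks are dropped after the start.
- **Primary model (Data analysis).** Poisson counts with an offset for time on ward: "we will use fixed effects for secular trend, and a random effect for ward". The intervention term is not written out. Power is stated for one pre-to-post difference of 12–28%.
- **Change over time (Data analysis).** Secondary analysis (i) is "to investigate changes in outcomes over time". It does not say whether time means calendar time or time since the ward started.
- **Implementation (train-the-trainer section).** Site leads' duties include "supporting nursing unit managers to iteratively co-design their ward action plan with the ward clinicians to implement and embed the intervention", and top-up training as needed.

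**The concern.** Ward action plans are revised after the start, so an effect that builds as practice beds in is plausible. One that fades as attention moves on is also plausible. Strengths and limitations says adherence will not be measured quantitatively, so no adherence data would show build-up or fade.

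In a stepped wedge, a model with one constant effect does not average the effects at different lengths of exposure. Once every ward is on, the early wards' longest exposure acts as the comparator for the wards that have just started, and its weight can turn negative. A growing benefit is then partly subtracted from itself, and a fading one is inflated. The effect on the primary outcome also feeds the benefit-to-cost ratio and its threshold of 1.

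**Working it through.** **1. The plan's own figure.** The article gives no alpha or power for the 12–28%. Assume 5% two-sided. A two-sample Poisson log rate ratio, with 244,800 bed days split evenly and clustering ignored, detects 12.3% (8/1000) to 23.8% (2/1000) at 80% power, and 14.1% to 27.3% at 90%. A standard stepped-wedge variance gives about 23% and 46–47% at 80%. Neither returns 12–28% at one power level. Nothing below depends on this figure; it matters here only because it refers to a single pre-to-post difference.

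**2. Inputs.**
- Three sequences of 8 wards. This assumes one ward per hospital in each sequence, as Fig. 2 is not shown.
- 17 + 51 = 68 weeks, or four 17-week blocks: the first all control, the last all intervention.
- 244,800/(24 × 68) = 150 bed days and 48,960/(24 × 68) = 30 episodes per ward-week.
- ICC 0.03–0.08 and 2–8 events per 1000 bed days, both from Data analysis. The scale of the ICC is not stated, so several readings are shown.

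**3. Hand check (four blocks, no weeks dropped, ward effect dominant).** Centre the on/off indicator as x − row mean − column mean + grand mean. In twelfths, with the exposure block in brackets:

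| Sequence | Block 1 | Block 2 | Block 3 | Block 4 |
|---|---|---|---|---|
| 1 | −3 | +5 (1st) | +1 (2nd) | −3 (3rd) |
| 2 | 0 | −4 | +4 (1st) | 0 (2nd) |
| 3 | +3 | −1 | −5 | +3 (1st) |

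The treated cells sum to 10. The weights are (5+4+3)/10 = 1.2, (1+0)/10 = 0.1 and −3/10 = −0.3.

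**4. Weekly grid with the three pre-start weeks dropped.** These are generalised least squares weights with a random ward intercept. λ is the ratio of ward variance to weekly residual variance:
- ICC on the episode or bed-day scale: λ = m·ICC/(1 − ICC). This runs from 30 × 0.03/0.97 = 0.93 to 150 × 0.08/0.92 = 13.0.
- ICC read as a log-scale ward variance: λ = variance × events per ward-week. This runs from 0.03 × 0.3 = 0.009 to 0.08 × 1.2 = 0.096.

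| Reading | Weights, week as a category | Weights, linear trend | SE of exposure average ÷ SE of constant effect |
|---|---|---|---|
| Log variance 0.03, 2/1000 | 0.90 / 0.19 / −0.09 | 0.87 / 0.21 / −0.08 | 1.21, 1.18 |
| Log variance 0.08, 8/1000 | 1.16 / 0.10 / −0.26 | 1.10 / 0.13 / −0.23 | 1.45, 1.35 |
| ICC 0.03, episodes | 1.25 / 0.07 / −0.32 | 1.18 / 0.11 / −0.29 | 1.59, 1.42 |
| ICC 0.08, bed days | 1.26 / 0.07 / −0.33 | 1.19 / 0.10 / −0.29 | 1.61, 1.44 |

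**5. Effect on the estimate.** The estimated rate ratio is exp(Σ weight × ln RR). Use ln 0.95 = −0.0513, ln 0.85 = −0.1625 and ln 0.75 = −0.2877.
- *Reductions of 5/15/25%.* The mildest weights (0.898/0.189/−0.087) give −0.0461 − 0.0307 + 0.0250 = −0.0518, so 0.95. Weights 1.2/0.1/−0.3 give −0.0616 − 0.0163 + 0.0863 = +0.0085, so 1.01. The most extreme row gives 1.02. The true average is exp(−0.5015/3) = 0.846.
- *Reductions of 25/15/5%.* The mildest weights give 0.75 to 0.76. Weights 1.2/0.1/−0.3 give −0.3452 − 0.0163 + 0.0154 = −0.3461, so 0.71. The most extreme row gives 0.70. The true average is again 0.846.
- *Steady growth, 7/14/20%.* 0.93 to 0.97, against a true average of 0.80^(2/3) = 0.86.
- *No effect in the first block.* True ratios of 1.00/0.89/0.80 give 0.99 to 1.07, and 1.00/1.00/0.80 give 1.02 to 1.08.
- *Constant effect.* The weights sum to 1, so it is recovered exactly.

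**6. With a separate effect per exposure block.** The three effects, and hence their average, are recovered without bias under every pattern. The SE ratios are in the last column of the table in step 4.

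**The case against.** The strongest reply is that this is a condensed article which promises an analysis plan before data lock, and that detail on a secondary analysis belongs there. That stands as far as absence of detail goes. But the article itself fixes the coding, the window and the single contrast, and the negative weight follows from those.

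Other points also stand in part:
- The constant effect is inferred from the pre/post coding and the power sentence. It is not written out. Secondary analysis (i) may already be meant as an exposure-time analysis.
- No passage predicts a lagged effect. Training and preparation come before each start and three pre-start weeks are dropped. Growth is plausible, not established.
- Weights near 1.2/0.1/−0.3 are one end of a range. With small ward variance and rare events the distortion is milder.
- If the three pre-trial years were put into the model, the last weight would shrink to −0.07 (week as a category) or become +0.13 (linear trend). The article plans those data only for examining seasonality and unusual variation.

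A reader might infer that an effective intervention is likely to be declared harmful. The documents do not support that. Steady growth keeps the direction of benefit, and the point estimate passes 1 mainly when there is little or no effect in the first 17 weeks. Even at an assumed 15 events per 1000 bed days and log-scale ward variance 0.16, a 5/15/25% pattern gives about 3.5% significant harm, against 2.5% with no effect. What is lost is power. At the same assumed inputs, 300 simulated trials per pattern detected benefit in 1% for 5/15/25% and in 71% for a constant 15%.

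**Conclusion.** The point holds as a weakness that is cheap to mend, not as an error that invalidates the primary analysis. The weight on exposure weeks 35–51 is negative in every case computed within the 68-week window, from about −0.08 to −0.33, under either form of trend. The consequence is dilution of a growing effect and overstatement of a fading one, by the amounts in the working.

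This rests on a constant intervention effect being what is meant, on an even spread of wards over sequences, on 150 bed days per ward-week, and on a linear approximation to the Poisson model. How large the distortion is depends on the unstated ICC scale.

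A reader might go further and conclude that a null primary result should be set aside whenever an exposure-time model looks better. That does not follow. The averaged effect is less precise, the two estimates will often differ by chance even when the effect is constant, and such a rule would rescue null results without restraining an overstated fading effect.

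**What to change.** Leave the primary model as it is. In the analysis plan:

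1. Define secondary analysis (i) as an exposure-time sensitivity analysis: the same Poisson mixed model, with a separate intervention effect for exposure weeks 1–17, 18–34 and 35–51.
2. Report the three rate ratios and their equally weighted average (on the log scale), with 95% confidence intervals, beside the constant-effect estimate.
3. Carry the average into the cost–benefit sensitivity analyses.
4. State that differences will be interpreted in both directions, growth and fade, and that no rule overrides the primary conclusion.

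The cost is some wording, one extra model fit, and an averaged effect whose standard error is about 1.2 to 1.6 times that of the primary estimate. The effect in the longest-exposure block is less precise still, with a standard error about 1.7 to 2.4 times as large.
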